**Sintilimab injection:**

On days 0-1 prior to each HAIC treatment, subjects will receive intravenous infusion of Sintilimab at a dose of 200 mg, administered once every 3 weeks (Q3W), until the subjects meet the criteria for study termination.

**HAIC：**

Based on the clinical routine experience of this research center, the FOLFOX regimen will be selected for HAIC, with the following doses: Oxaliplatin 85 mg/m^2^ infused over 2 hours, Leucovorin 400 mg/m^2^ infused over 2 hours, 5-Fu 400 mg/m^2^ bolus over 10 minutes, followed by continuous infusion of 5-Fu 1200 mg/m ^2^ over 23 hours. The first HAIC will be implemented on the date predetermined by the investigator, followed by once every 3 weeks, and the number of subsequent HAIC treatments will be conducted as needed based on the actual condition of the patient as determined by the investigator.

## Dose adjustment/suspension of medication

**donafenib tablets:**

1) The initial dose adjustment scheme is 200 mg bid

During the treatment period, if the subject experiences grade 4 hematologic toxicity or grade 3 non-hematologic toxicity related to the investigational drug, the medication will be temporarily suspended (according to NCI CTCAE V5.0 standards), only allowing the subject to undergo a maximum of 2 dose adjustments. If grade 4 hematologic toxicity or grade 3 non-hematologic toxicity cannot return to normal or CTCAE grade 1 within 2 weeks after suspension, the medication will be permanently discontinued. (Grade 3 or higher adverse reactions do not include alopecia, uncontrolled nausea/vomiting, uncontrolled allergic reactions, and asymptomatic laboratory test abnormalities)

After the first suspension of medication, if the adverse reactions recover to ≤ Grade 1 within 1 week, continue taking the original dose; If recovery to ≤ Grade 1 occurs within 2 weeks of drug suspension, the dose is reduced to 200 mg qd to continue treatment; After dose adjustment, if drug suspension occurs again, and recovery to ≤ Grade 1 occurs within 2 weeks, the dose is reduced to 200 mg qod to continue treatment. If grade 4 hematologic toxicity or grade 3 non-hematologic toxicity occurs again (the 3rd occurrence), the drug will be permanently discontinued. That is Dose adjustment plan:

| Initial dose | First dose reduction | Second dose reduction |
| --- | --- | --- |
| 200 mg bid | 200 mg qd | 200 mg qod |

2) Dose adjustment scheme when the initial dose is adjusted to 100 mg bid due to DLT

If ≥2 cases of dose-limiting toxicity (DLT) are observed among the first 6 subjects, and the research team assesses that the toxicity is solely related to donafenib treatment, then the initial dose adjustment for subsequent enrolled patients receiving donafenib treatment will be 100 mg bid. At this time, the dose adjustment follows the same principles and processes as normal dose adjustments, with specific dose changes as follows:

| Initial dose | First dose reduction | Second dose reduction |
| --- | --- | --- |
| 100mg bid | 100mg qd | 100mg qod |

**Sintilimab injection:**

Throughout the study, dose adjustments for sintilimab are not permitted; the principles for pausing and permanently discontinuing sintilimab administration are outlined in Table 1.

If a subject experiences a grade 2 drug-related irAE or a grade 3 or higher other AE (refer to the ESMO guidelines for the management of toxicity related to immune checkpoint inhibitors), the subject must suspend administration, with a maximum delay of 7 days; subsequent administration schedules will be adjusted accordingly. If the administration is delayed for more than 7 days, it will be considered a missed dose, and the subject will receive the next cycle of administration according to the original schedule (calculated from the date of the first administration). If treatment-related adverse reactions have not recovered to grade 0-1 or baseline levels within 6 weeks after the last dose of Sintilimab, then Sintilimab should be permanently discontinued. If a subject discontinues the medication for more than 6 weeks and the investigator determines that the risks of continuing administration outweigh the benefits, they may permanently withdraw from the study treatment.

If a subject requires a gradual reduction in dosage of steroids due to an adverse event, the recombinant humanized anti-PD-1 monoclonal antibody may be discontinued for a longer period until the steroid tapering is completed or reduced to a prednisone dose of ≤10 mg/day (or equivalent dose). If the discontinuation exceeds 6 weeks (with the maximum discontinuation time for sintilimab due to steroid tapering not exceeding 12 weeks), the investigator may reassess the overall risk-benefit evaluation before resuming the use of the recombinant humanized anti-PD-1 monoclonal antibody.

Subjects may interrupt administration for reasons other than toxic reactions (such as surgical procedures), with the interruption not exceeding 6 weeks. The investigator may restart the use of recombinant humanized anti-PD-1 monoclonal antibody *based on an overall risk-benefit assessment.*

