| **Dose adjustment scheme** | 1) Donafenib dose adjustment scheme: If grade 4 hematologic toxicity or grade 3 non-hematologic toxicity occurs, temporarily discontinue the drug (according to NCI CTCAE V5.0 standards). After the first suspension of medication, if the adverse reactions recover to ≤ Grade 1 within 1 week, continue taking the original dose; If recovery to ≤ Grade 1 occurs within 2 weeks of suspension, then reduce the dose to 200 mg qd; If the dose is adjusted and medication is suspended again, if recovery to ≤ Grade 1 occurs within 2 weeks, then reduce the dose to 200 mg qod, with a maximum of 2 dose adjustments allowed. If recovery to normal or CTCAE Grade 1 cannot be achieved within 2 weeks after stopping the medication, then permanently discontinue the medication. If Grade 4 hematologic toxicity or Grade 3 non-hematologic toxicity occurs again (the 3rd occurrence), then permanently discontinue the medication.  At an initial dose of 200 mg bid, the dose adjustment scheme is as follows:   \| Initial dose \| First dose reduction \| Second dose reduction \| \| --- \| --- \| --- \| \| 200mg bid \| 200mg qd \| 200mg qod \|   If the initial dose of donafenib is adjusted to 100 mg bid due to the observation of ≥2 cases of DLT in the first 6 patients, the dose adjustment principles will be consistent with those at 200 mg bid, and the specific dose adjustment scheme is as follows:   \| Initial dose \| First dose reduction \| Second dose reduction \| \| --- \| --- \| --- \| \| 100mg bid \| 100mg qd \| 100mg qod \|  1. **Sintilimab dose adjustment scheme**: Dose adjustment of sintilimab is not permitted throughout the study; when intolerable toxicity related to sintilimab occurs, the investigator may decide to suspend or permanently discontinue sintilimab administration.   If a subject experiences a grade 2 drug-related irAE or a grade 3 or higher other AE (refer to the ESMO guidelines for the management of toxicity related to immune checkpoint inhibitors), the subject must suspend the administration of Sintilimab, with a maximum delay of 7 days; the subsequent administration schedule will be adjusted accordingly. If the administration is delayed for more than 7 days, it will be considered a missed dose, and the subject will receive the next cycle of administration according to the original schedule (calculated from the date of the first administration of Sintilimab). If treatment-related adverse reactions have not recovered to grade 0-1 or baseline levels within 6 weeks after the last dose of Sintilimab injection, the administration of Sintilimab injection should be permanently discontinued. Additionally, if the subject discontinues the medication for more than 6 weeks and the investigator determines that the risks of continuing treatment outweigh the benefits, the subject must permanently discontinue Sintilimab.  3) HAIC: In the HAIC chemotherapy regimen, only the dose of Oxaliplatin will be adjusted. That is: when the tumor diameter > 10 cm and there is abundant blood supply, the dose of Oxaliplatin selected is 130 mg/m^2^. For tumors ≤ 10 cm and with less abundant blood supply, the dose of Oxaliplatin selected is 85 mg/m^2^. Additionally, when a large tumor significantly shrinks after several courses of HAIC treatment, a dose reduction may be appropriate, even down to 60 mg/m^2^. Subsequent researchers can make appropriate dose adjustments based on the patient's actual treatment situation and tolerance, and ensure proper documentation.  ***Note**: If a subject permanently discontinues one of the investigational drugs (Donafenib or Sintilimab) due to adverse reactions, and the investigator assesses that the subject may still benefit from continuing the other drug in combination with HAIC treatment, the subject may receive treatment with the other drug in combination with HAIC in this study. If a subject permanently discontinues both drugs due to adverse reactions, the subject must permanently withdraw from the study treatment. |

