| Recurrent or persistent adverse reactions | Recurrent grade 3 or 4 (excluding endocrine disorders)  Grade 2 or 3 adverse reactions within 12 weeks after the last administration  Not improved to grade 0-1 (excluding endocrine disorders)  Corticosteroids failed to reduce to ≤ 10 mg/day of prednisone equivalent within 12 weeks after the last administration. | Permanent discontinuation |

a: Resume administration after symptom improvement to grade 0-1 or baseline level.

*The safety of reinitiating Sintilimab treatment after myocarditis improves to grade 0-1 is still unclear.

b: Pituitary inflammation, adrenal cortical insufficiency, hypothyroidism/thyroid dysfunction, and type 1 diabetes can be re-administered when adequately controlled and requiring only physiological hormone replacement therapy.

c: The safety of resuming treatment with this product after myocarditis improves to grade 0-1 is still unclear.

d: For grade 4 laboratory abnormalities, the decision to discontinue medication should be based on accompanying clinical symptoms/signs and according to the clinical judgment of the investigator.

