2. ECOG PS score collection. If it is conducted within 3 days prior to the first administration, there is no need to repeat the collection on day 1 of the monotherapy period with donafenib ;
3. Investigational drug treatment (donafenib monotherapy);
4. Dispense the treatment drug for the donafenib monotherapy period;
5. Conduct DLT observation after administration: applicable only to patients entering the safety induction phase, i.e., the first 6 patients enrolled;
6. Collect concomitant medication/treatment;
7. Collect adverse events: the adverse events of subjects must be closely monitored throughout the entire research process.
   1. Combination treatment period (the first use of Sintilimab is designated as CIDI, with visits every 3 weeks, time window ±3 days)

After 3-7 days of monotherapy with donafenib , if the subjects are well-tolerated to donafenib during the monotherapy period as assessed by the investigator, subsequent subjects may receive intravenous infusion treatment with Sintilimab injection, and begin approximately 1 day of HAIC treatment on the same day or the day after the infusion of Sintilimab.

All visits during the combination treatment period will be scheduled according to the appropriate calendar days starting from the combination treatment period C1D1 (the day of first use of Sintilimab), with a treatment cycle of every 3 weeks (the length of the 3-week cycle is fixed, regardless of whether the investigational drug is paused). An allowable visit time window of ±3 days is permitted. If at any time during the study the treatment with the investigational drug is paused, all study visits, safety, and efficacy assessments should continue according to the evaluation schedule based on the appropriate calendar days from the combination treatment period C1D1. All data obtained from these assessments must be supported by the original records of the patient. The CRF does not serve as the original record.

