1. CT/MRI Examination: CT/MRI examination once every 6 weeks (relative to the combination treatment period C1D1, time window ±3 days). Chest and abdomen must be examined; other sites should only undergo CT/MRI examination if there are clinical indications of metastasis. During the study period, the same imaging techniques (scanning equipment and methods as well as imaging parameters) used at baseline must be employed, and the measurement methods must remain consistent with baseline, ideally assessed by the same investigator. If the investigator suspects that the subject may have progression, an unscheduled CT/MRI examination may be conducted; if the unscheduled examination does not reveal progression, subsequent evaluations should be conducted as close as possible to the originally scheduled examination time. If the subject confirms disease progression, subsequent CT/MRI examinations will no longer be required.
2. Safety data: **CIDI does not require repeated safety checks, only when the subject has corresponding clinical indications or the investigator deems it necessary.** Safety checks from C2D1 onwards must be completed before each administration of Sintilimab, and the blood collection time cannot be earlier than 3 days before administration. The results must be determined by the investigator to meet the criteria for continued medication before treatment can begin. The collection items are the same as during the screening period, except for the following items:

- A limited physical examination based on symptoms should be conducted; height measurement is not necessary.
- Virological testing: HBV DNA testing is only performed on known HBV-positive patients, and HCV RNA testing is only performed on known HCV-positive patients;
- Thyroid function tests: If there are clinically significant changes in thyroid function during treatment, it is recommended to consult the endocrinology department and rule out pituitary dysfunction;
- Cardiac ultrasound: Only performed if the subject has clinical indications (such as abnormal ECG, chest tightness, cyanosis, dyspnea, etc.) or if deemed necessary by the investigator;

1. AFP testing: **No need for repeat testing during combination therapy period C1D1;**
2. ECOG PS score collection: **No need for repeat testing during combination therapy period C1D1;**
3. Investigational drug treatment: donafenib + Sintilimab;
4. HAIC treatment: Infusion of sintilimab starts on the same day or the second day

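### Sintilimab hold rules conflict: a 6-week recovery limit in the text against 12 weeks in Table 1, and, separately, two possible dosing calendars after a delay of 7 days or less

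*Protocol*

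**What the plan says.** **Recovery limit.** Section 5.3 (Sintilimab injection) requires a permanent stop when treatment-related reactions "have not recovered to grade 0-1 or baseline levels within 6 weeks after the last dose of Sintilimab, then Sintilimab should be permanently discontinued". The dose adjustment row of the Protocol Summary has the same condition: "have not recovered to grade 0-1 or baseline levels within 6 weeks after the last dose of Sintilimab injection". Neither mentions endocrine events. Section 5.3 also states that the "principles for pausing and permanently discontinuing sintilimab administration are outlined in Table 1".

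The last row of Table 1, on recurrent or persistent reactions, lists as grounds for a permanent stop "Grade 2 or 3 adverse reactions within 12 weeks after the last administration", followed on the next line by "Not improved to grade 0-1 (excluding endocrine disorders". A separate item in that row covers steroids that could not be tapered within 12 weeks. Footnote a allows dosing to resume on recovery to grade 0-1 or baseline. Footnote b allows it for listed endocrine conditions once they are controlled on physiological replacement alone. Neither footnote carries a 6-week cap.

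**Dosing calendar.** For the events that require a hold, section 5.3 allows suspension "with a maximum delay of 7 days; subsequent administration schedules will be adjusted accordingly". A longer delay counts as a missed dose, and dosing returns to the original calendar. Section 6.3 (combination therapy period) counts everything from C1D1 and says that "the length of the 3-week cycle is fixed, regardless of whether the investigational drug is paused", with a ±3-day visit window. The trial flowchart places sintilimab on those cycle-day-1 visits. Section 5.2 gives sintilimab 0-1 days before each HAIC course.

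**The concern.** These are operative rules on when a patient leaves the PD-1 antibody for good and how soon the next dose follows a short hold. If two parts of one protocol give different answers, the decision depends on which page the investigator consults. Table 1 foresees suspensions for many grade 2 and 3 reactions, so the situation is an expected one. With 30 patients, a few decisions taken under different rules could visibly change how sintilimab exposure and discontinuation are described.

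The rules belong to the protocol's treatment section. They are not something that would normally be left to a statistical analysis plan.

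**Working it through.** No sample size, power or alpha is involved. The check compares the passages and counts days.

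**1. Reading the Table 1 row.** The 12-week item is split over two lines in the extracted text. Read literally, the first line would make any grade 2 or 3 reaction within 12 weeks a reason for a permanent stop. That would contradict the many grade 2 and 3 entries in the same table that only suspend dosing. Joined, the lines say that a grade 2 or 3 reaction not improved to grade 0-1 within 12 weeks of the last administration, endocrine disorders excepted, leads to a permanent stop. This is the only workable reading.

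**2. Recovery limit.** Take the last dose as day 0. The limits are 6 × 7 = 42 days (text) and 12 × 7 = 84 days (Table 1). For a non-endocrine reaction that Table 1 lists for suspension, with no steroid taper:

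| Recovery after last dose | Section 5.3 text and Summary | Table 1 |
|---|---|---|
| By week 6 | resume | resume |
| After week 6, by week 12 (e.g. week 8) | stop permanently | may resume |
| After week 12 | stop permanently | stop permanently |

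Doses falling due before the limit number one under 6 weeks (day 21) and three under 12 weeks (days 21, 42 and 63).

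For an endocrine event that is controlled on replacement but not back to grade 0-1 or baseline at 6 weeks, the text stops sintilimab and footnote b permits re-administration. This conflict does not depend on the split row.

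**3. Calendar after a short delay.** Take C1D1 as day 0, with a dose due on day 21 and given *d* days late.
- Shifted schedule (section 5.3): next dose on day (21 + d) + 21, a gap of 21 days.
- Fixed cycle (section 6.3): next dose on day 42, a gap of 42 − (21 + d) = 21 − d days.

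| Delay d (days) | Given on day | Next dose, shifted (gap) | Next dose, fixed (gap) | Shift beyond ±3 days? |
|---|---|---|---|---|
| 1 | 22 | day 43 (21) | day 42 (20) | no |
| 3 | 24 | day 45 (21) | day 42 (18) | no |
| 4 | 25 | day 46 (21) | day 42 (17) | yes |
| 6 | 27 | day 48 (21) | day 42 (15) | yes |
| 7 | 28 | day 49 (21) | day 42 (14) | yes |

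For delays above 7 days both sections return to the original calendar, so they agree. Because sintilimab is tied to the day of HAIC or the day before it, the interval between any HAIC courses given alongside moves as well.

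**The case against.** **On the recovery limit.** Section 5.3 itself allows up to 12 weeks for holds caused by steroid tapering, and corticosteroids are a named treatment for immune-related events. Some long holds are therefore already consistent with Table 1. That stands, but the allowance is limited to tapering and has its own item in the table. It does not explain the separate 12-week item for reactions that have not improved. One could also say that the stricter rule governs, but no section says so.

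A reader might infer that every reaction resolving between weeks 6 and 12 is handled in opposite ways. The documents do not support that. Taper holds are aligned, Table 1 stops several events at onset (for example grade 3 or 4 pneumonia or myocarditis), and the table's 12-week item does not apply to endocrine events.

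**On the calendar.** Section 6.3 can be read as fixing visits and assessments only, since its sentence on pauses concerns those. Section 5.3 would then be the specific dosing rule. This is a fair reading, and it reduces the point to a clarification. It does not remove it, because section 6.3 describes the fixed unit as the treatment cycle and the flowchart puts sintilimab on those visits. On this reading, shifts of 4-7 days also take dosing outside the ±3-day visit window.

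A reader might further infer that patients could be dosed on outdated safety bloods. Section 6.3 rules this out: from C2D1, checks precede each administration and "the blood collection time cannot be earlier than 3 days before administration". Bloods are already tied to the actual dose.

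**On consequences.** It would go too far to call sintilimab exposure uninterpretable. Section 5.4.5 requires the dose and timing of each infusion, and the reasons for delays and missed doses, to be recorded in the CRF. No effect on ORR is shown.

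**Conclusion.** Both points hold within limits, and the first is the stronger.

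The 6-week and 12-week stopping rules contradict each other for non-endocrine reactions that Table 1 lists for suspension, held without a steroid taper, that recover after week 6 and by week 12. For endocrine events the conflict is the missing exception in the text against footnote b. The 12-week reading rests on rejoining the split row.

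The calendar point is smaller. For delays of 7 days or less, the fixed cycle gives a next interval of 20 to 15 days for delays of 1-6 days and 14 days for a full 7-day delay, against 21 days on the shifted schedule. The 14-day figure is the extreme case and assumes that section 6.3 governs dosing as well as assessments.

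It might be inferred that one patient meets both problems in sequence. That is not so: stop-or-resume concerns holds lasting past 6 weeks, and the 14-or-21-day question concerns delays of at most 7 days. The two branches within section 5.3 (up to 7 days, and longer) do not conflict with each other. The calendar conflict is between section 5.3 and section 6.3 with the flowchart.

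The documents do not show which limit or calendar was intended, and no view is taken on that.

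**What to change.** - Reconcile the Protocol Summary and the section 5.3 text with the last row and footnotes of Table 1, so that one recovery limit and one statement on endocrine events appear throughout.
- Reconcile the rule in the Summary and section 5.3 that later doses move after a delay of up to 7 days with the fixed cycle in section 6.3 and the flowchart. State one anchor for later sintilimab and HAIC doses, and say whether the C1D1 calendar governs dosing or assessments only.

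The clinical team must choose the limit and the anchor. The existing pre-dose blood-sampling rule needs no change. The cost is a wording amendment in those places, with no assessments beyond those already required before each dose.

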**Table 1 Sintilimab Dose Adjustment Scheme**

| Sintilimab-related adverse events | Severity | Dose adjustment |
| --- | --- | --- |
| Pneumonia | Grade 2 | Suspend administration ^a^ |
|  | Grade 3 or 4 or recurrent Grade 2 | Permanent discontinuation |
| Diarrhea/Colitis | Grade 2 or 3 | Suspend administration ^a^ |
|  | Grade 4 | Permanent discontinuation |
| Hepatitis | For subjects with baseline normal ALT, AST, or TBIL, a 2nd grade increase in AST, ALT (3-5 times ULN) or TBIL (1.5-3 times ULN); For subjects with baseline AST, ALT, or TBIL > ULN, an increase in AST, ALT, or TBIL ≥ 50% (meeting the 2nd grade requirement) and a duration of < 7 days. | Suspend administration ^a^ |
|  | For subjects with baseline normal ALT, AST, or TBIL, a 3rd or 4th grade increase in AST, ALT (> 5 times ULN) or TBIL (> 3 times ULN); For subjects with baseline AST, ALT, or TBIL > ULN, an increase in AST, ALT, or TBIL ≥ 50% (meeting the 3rd or 4th grade requirement) and a duration of ≥ 7 days. | Permanent discontinuation |
| Nephritis | Grade 2 or 3 elevation of serum creatinine | Suspend administration ^a^ |
|  | Grade 4 elevation of serum creatinine | Permanent discontinuation |
| Endocrine diseases | Symptomatic Grade 2 or 3 hypothyroidism  Grade 2 or 3 hyperthyroidism  Grade 2 or 3 pituitary inflammation  Grade 2 adrenal insufficiency  Grade 3 hyperglycemia or Type 1 diabetes | Suspend administration ^b^ |
|  | Grade 4 hypothyroidism  Grade 4 hyperthyroidism  Grade 4 pituitary inflammation  Grade 3 or 4 adrenal insufficiency  Grade 4 hyperglycemia or type 1 diabetes | Permanent discontinuation |
| Dermatological adverse reactions | Grade 3 | Suspend administration ^a^ |
|  | Grade 4, Stevens-Johnson syndrome (SJS) or toxic epidermal necrolysis (TEN) | Permanent discontinuation |
| Thrombocytopenia | Grade 3 | Suspend administration ^a^ |
|  | Grade 4 | Permanent discontinuation |
| Other immune-related adverse reactions | Grade 3 or 4 elevated amylase or lipase  Grade 2 or 3 pancreatitis  Grade 2 myocarditis ^c^  Other immune-related adverse reactions of grade 2 or 3 occurring for the first time | Suspend administration ^a^ |
|  | Grade 4 pancreatitis or any grade of recurrent pancreatitis  Grade 3 or 4 myocarditis  Grade 3 or 4 encephalitis  Other immune-related adverse reactions of grade 4 occurring for the first time ^d^ | Permanent discontinuation |
| Recurrent or persistent adverse reactions | Recurrent grade 3 or 4 (excluding endocrine disorders)  Grade 2 or 3 adverse reactions within 12 weeks after the last administration  Not improved to grade 0-1 (excluding endocrine disorders)  Corticosteroids failed to reduce to ≤ 10 mg/day of prednisone equivalent within 12 weeks after the last administration. | Permanent discontinuation |

a: Resume administration after symptom improvement to grade 0-1 or baseline level.

*The safety of reinitiating Sintilimab treatment after myocarditis improves to grade 0-1 is still unclear.

b: Pituitary inflammation, adrenal cortical insufficiency, hypothyroidism/thyroid dysfunction, and type 1 diabetes can be re-administered when adequately controlled and requiring only physiological hormone replacement therapy.

c: The safety of resuming treatment with this product after myocarditis improves to grade 0-1 is still unclear.

d: For grade 4 laboratory abnormalities, the decision to discontinue medication should be based on accompanying clinical symptoms/signs and according to the clinical judgment of the investigator.

